## Abstract

**Background:**

Despite current advances in cancer treatment, many breast cancer survivors still face long-term post-operative challenges as a result of suffering from daily pain and other distressing symptoms related to lymphedema, ie, abnormal accumulation of lymph fluid in the ipsilateral upper limb or body. Grounded in research-driven behavioral strategies, The-Optimal-Lymph-Flow is a unique Web- and mobile-based system focusing on self-care strategies to empower, rather than inhibit, how breast cancer survivors manage daily pain and symptoms. It features a set of safe, feasible, and easily-integrated-into-daily-routine exercises to promote lymph flow and drainage, as well as guidance to maintain an optimal body mass index (BMI).

**Objective:**

To conduct a randomized clinical trial (RCT) to evaluate the efficacy of the Web- and mobile-based The-Optimal-Lymph-Flow system for managing chronic pain and symptoms related to lymphedema. The primary outcome includes pain reduction, and the secondary outcomes focus on symptom relief, limb volume difference by infra-red perometer, BMI, and quality of life (QOL) related to pain. We hypothesize that participants in the intervention group will have improved pain and symptom experiences, limb volume difference, body mass index, and QOL.

**Methods:**

A parallel RCT with a control-experimental, pre- and post-test, repeated-measures design is used in this study. A total of 120 patients will be randomized according to the occurrence of pain. Participants will be recruited face-to-face at the point of care during clinical visits. Participants in the intervention group will receive the Web- and mobile-based The-Optimal-Lymph-Flow intervention and will have access to and learn about the program during the first in-person research visit. Participants in the control group will receive the Web- and mobile-based Arm Precaution program and will have access to and learn about the program during the first in-person research visit. Participants will be encouraged to enhance their learning by accessing the program and following the daily exercises during the study period. Participants will have monthly online self-report of pain and symptoms at 4 and 8 weeks post-intervention. During the two in-person research visits prior to and 12 weeks post-intervention, participants will be measured for limb volume difference, BMI, and complete self-report of pain, symptoms, self-care behaviors, and QOL.

**Results:**

This trial is currently open for recruitment. The anticipated completion date for the study is July 2017. The primary endpoint for the study is absence or reduction of pain reported by the participants at week 12 post-intervention.

**Conclusions:**

The-Optimal-Lymph-Flow is a unique Web- and mobile-based self-care and patient-reported outcome system designed to effectively help women treated for breast cancer manage daily pain and symptoms related to lymphedema. Patients learn self-care strategies from a Web- and mobile-based program and track their symptoms. The RCT will directly benefit all women treated for breast cancer who suffer from or at risk for pain and symptoms related to lymph fluid accumulation.

**Trial Registration:**

Clinicaltrials.gov NCT02462226; https://clinicaltrials.gov/ct2/show/NCT02462226 (Archived by WebCite at http://www.webcitation.org/6du4IupG5)

##  Introduction

### Background

Annually, more than 230,000 women are diagnosed with breast cancer, and currently there are more than 2.9 million breast cancer survivors in the United States [1]. Even years after cancer treatment, about 20-40% of women treated for breast cancer suffer daily from chronic pain and more than 50% of women report multiple distressing symptoms related to lymphedema (ie, the abnormal accumulation of lymph fluid in the ipsilateral upper limb or body) [2-5]. The abnormal accumulation of lymph fluid or lymphedema after breast cancer treatment is a result of obstruction or disruption of the lymphatic system associated with cancer treatment (eg, removal of lymph nodes and/or radiotherapy), influenced by patient personal factors (eg, obesity or higher body mass index [BMI]), and triggered by factors such as infections or trauma [6-8].

Breast cancer survivors without a diagnosis of lymphedema also suffer from pain (40%), tenderness (47.3%), aching (30%), or soreness (32.7%); however, significantly higher number of breast cancer survivors with lymphedema experience pain (45.2%), tenderness (52.4%), aching (61.9%), or soreness (31%) in the ipsilateral upper limb or body [9]. In addition to pain, on average, breast cancer survivors without lymphedema report about 5 distressing symptoms while breast cancer survivors with lymphedema report 10 distressing symptoms related to the accumulation of lymph fluid [9-10]. It is clear that many breast cancer survivors still face long-term post-operative challenges as a result of suffering from daily pain and other distressing symptoms related to lymphedema, despite current advances in cancer treatment.

Pain and symptoms related to the accumulation of lymph fluid following breast cancer treatment remain as the main debilitating late complications that impact the breast cancer survivors’ quality of life [2,3,5,11]. Persistent pain related to cancer treatment is considered a stressful complication since it is perceived as a constant reminder of cancer [2,12] and exerts tremendous limitations on breast cancer survivors’ daily living [2,5]. Pain and other distressing symptoms related to lymphedema following cancer treatment can instigate fears and induce feelings of loss of control [2,3,5]. Specifically, the experience of pain, including tenderness, aching, or soreness, causes significant and unrelenting distress among breast cancer survivors [3]. Such distress is usually heightened when breast cancer survivors expect pain and symptoms related to lymphedema to disappear but instead stay as a “perpetual discomfort” [3]. The negative impact of pain and symptoms related to lymphedema can be a source of considerable disability and psychological distress that negatively influences the patient’s daily living [2,3,11,12], and creates a tremendous burden on the health care system [13]. Nonetheless, in clinical practice pain and symptoms related to lymphedema are still under-recognized and undertreated.

While more research is needed to explore the exact etiology of persistent pain and other symptoms after breast cancer treatment,(eg, arm swelling, breast swelling, chest wall swelling, heaviness, firmness, tightness, stiffness, numbness, burning, stabbing, tingling, and limited limb movement), physiologically, the accumulation of lymph fluid in the affected area or limb may create undue pressure on nerves, producing feelings of pain, aching, tenderness, soreness, burning, tingling, stabbing, and numbness as well as inducing sensations of swelling, heaviness, tightness, and firmness [14-15]. Accumulated lymph fluid in the affected area or limb also leads to stiffness and limited limb movement of arm, shoulder, fingers, and elbow [10,15]. Significant associations are found between pain (including aching and tenderness) and accumulation of lymph fluid in the ipsilateral upper limb [10,15]. Research has also shown that with increased number of symptoms reported, breast cancer survivors’ limb volume increased [10,15]. Limb volume as detected by the infra-red perometer has significantly elevated as breast cancer survivors’ reports of pain, tenderness, aching, swelling, heaviness, firmness, and tightness have increased [10]. On average, breast cancer survivors reported 4 symptoms for those with <5.0% limb volume increase; 5 symptoms for 5.0-9.9% limb volume increase, 7 symptoms for 10.0-14.9% limb volume increase, and 13 symptoms for >15% limb volume increase, respectively (*P*<.001) [10].

Breast cancer survivors are known to have a compromised lymphatic system due to breast surgery, dissection of lymph nodes and vessels, and radiation, which leads to ineffective lymphatic drainage, thus accumulated lymph fluid in the affected area or limb [10,15,16]. In addition to the risk factor of compromised lymphatic drainage from cancer treatment, higher BMI is also an established risk factor for the accumulation of lymph fluid [6-10]. Physiologically, a larger body mass creates a disproportion in lymph transport and capacity, resulting in excess extracellular fluid [6,17]. Women are 1.11 times more at risk for developing lymphedema with every increase of 1kg/m^2^ in their BMI [6-8,16]. Although the known risk factors for symptoms related to accumulation of lymph fluid directly from cancer treatment cannot be avoided, (such as removal of lymph nodes, surgery, radiation, chemotherapy, and hormonal therapy), some risk factors, (such as compromised lymphatic drainage and higher BMI), can be modified through education and self-care strategies [14,18,19].

Patient education focusing on self-care strategies holds great promise for reducing the risk of lymph fluid accumulation [14,18,19]. Research evidence demonstrates that even after controlling for confounding cancer treatment-related risk factors, patient education on self-care strategies remains an important predictor for patient-centered outcomes, including symptom experience and self-care behaviors [14,18,19]. Risk factors, such as compromised lymphatic drainage and higher BMI, can also be modified through self-care strategies [14,19]. Current patient education emphasizes precautionary lifestyle behaviors, such as avoidance of repetitive limb movement, lifting weighted objects, needle punctures, blood draw, and the use of compression garments for air travel in the affected limb [20,21]. To date, there is a paucity of high quality evidence to support these precautionary practices that reduce the risk of lymphedema and relieve pain or symptoms related to lymph fluid accumulation [20,21]. Research is lacking to provide evidence to reduce pain and symptoms related to lymph fluid accumulation through self-care strategies targeting compromised lymphatic drainage and higher BMI.

Grounded in research-driven self-care behavioral strategies [14,19], The-Optimal-Lymph-Flow [22] is a unique patient-centered Web- and mobile-based educational and behavioral program focusing on self-care strategies to lessen the symptom burden by promoting lymph flow and maintaining optimal BMI, targeting compromised lymphatic system and BMI, that is, risk factors for pain and symptoms related to lymph fluid accumulations. Patients learn self-care stratigies through the Web- and mobile-based program which can be downloaded on computer, laptop, as well as any mobile phones and tablets. Its underlying premise is to empower, rather than inhibit, how breast cancer survivors live their lives by emphasizing “what to do,” rather than “what to avoid.” It features a safe, feasible, and easily-integrated-into-daily-routine self-care strategies that include shoulder mobility exercises to promote shoulder function, muscle-tightening breathing, muscle-tightening pumping exercises, and large muscle exercises to promote lymph flow and drainage, as well as general instructions to encourage nutrition-balanced (more vegetables and fruits), portion-appropriate diet (feeling 75% full for each meal), adequate hydration, and sleep to strive for maintaining optimal BMI. Patients can learn and follow all the exercises through avatar video simulations [14,19]. The efficacy of The-Optimal-Lymph-Flow has been demonstrated in our recently published study of 140 patients who received the face-to-face nurse-delivered program [19]. Findings of the study demonstrated that over 90% of patients improved their limb volume at 12-month follow-up. This system has been used successfully for its usability testing. The preliminary usability tested was completed by 30 breast cancer survivors who evaluated the easiness, difficulties, and feasibility of using the system on computer, iPhone, iPad, or other smartphones or tablets. Findings of the usability and feasibility test have demonstrated that patients love the Web-based program, especially the videos using the avatar technology to demonstrate the complicated lymphatic system and illustrate the physiological functions of each exercise and detailed step-by-step instructions for each exercise.

The purpose of the research is to conduct a randomized clinical trial (RCT) to evaluate the efficacy of the Web- and mobile-based The-Optimal-Lymph-Flow system, a patient-centered educational and behavorial symptom management program focusing on promoting lymph flow and optimizing BMI, for managing chronic pain and symptoms related to lymphedema.

### Objectives and Hypotheses

The primary objective of this study is to determine the effectiveness of the Web- and mobile-based The-Optimal-Lymph-Flow system for managing chronic pain, aching, soreness, and tenderness among breast cancer survivors and quality of life related to pain. We hypothesize that participants in the intervention group will have no or less severe pain, aching, soreness, and tenderness, and better quality of life related to pain, aching, soreness, and tenderness in comparison with participants in the control group.

The secondary aim of the study is to evaluate the effectiveness of the Web- and mobile-basedThe-Optimal-Lymph-Flow system for managing symptoms related to lymph fluid accumulation, limb volume differences, and BMI. We hypothesize that participants in the intervention group will have fewer or less severe symptoms related to lymph fluid accumulation, minimal limb volume differences, and better BMI in comparison with participants in the control group.

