#### Outcome Measures

*Demographic and Medical Information*: a structured tool is used to gather demographic and medical information and is verified through reviewing participants’ medical records [14,17,19]. The demographic and medical information will be considered as covariates, including expectation of the program, pain medications, age, surgeries, lymph nodes procedure, radiation, chemotherapy, time since surgery, time since lymphedema diagnosis, and hormonal therapy.

*Primary and Secondary Outcome Measures*: primary measure focuses on pain which is assessed during prior to the intervention and week 12 post-intervention in-person visit, as well as week 4 and 8 post-intervention online assessment. Secondary measures include symptoms, limb volume difference by infra-red perometer, BMI, quality of life related to pain. Limb volume difference by infra-red perometer and BMI are only measured prior to and week 12 post-intervention in-person visits. Symptoms and quality of life related to pain are assessed prior to and week 12 post-intervention in-person visit as well as week 4 and 8 post-intervention online assessment.

*Pain and Symptoms Related to Lymphedema:* the Lymphedema and Breast Cancer Symptom Experience Index is a valid and reliable self-report tool to assess pain, including aching, soreness, tenderness, as well as symptoms related to lymphedema (ie, arm swelling, breast swelling, chest wall swelling, heaviness, firmness, tightness, stiffness, burning, stabbing numbness, tenderness, stiffness, redness, blistering, and tingling (pins and needles) [14,17,19]. Each symptom can be treated as categorical variable by choosing a “Yes” or “No” to indicate the presence or absence of a given symptom. Each item can also be rated on a Likert-type scale from 0 (no presence of a given symptom) to 4 (greatest severity of a given symptom). Higher scores indicate more severe symptom presence. A response frame of last three months will be used for all participants to ensure the chronicity of symptom presence during the first in-person visit.

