### Statistical Analysis

#### Primary Endpoint

The primary endpoint for the study is absence of pain or pain reduction reported by the participants at week 12 post-intervention.

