#### Sample Size and Power Calculations

We will enroll a total of 120 participants: 60 participants in The-Optimal-Lymph-Flow intervention and 60 participants in the Arm Precaution control group to account for a potential attrition of 20%, which has been observed in the prior studies in breast cancer survivors [10]. This will yield an adequate analytic sample size. Even with 20% attrition based on a 2 sample 2-sided *t* test with alpha=.05 and power of 90%, we can detect a difference of 0.7 standard deviations in the difference between the presence of pain in the intervention group compared to the control group at 8 weeks or at 12 weeks. The projected sample size will also provide sufficient statistical power for mixed regression models. For linear mixed models of continuous outcomes (eg, pain ratings), statistical power will exceed 80% to detect a medium effect, assuming a constant group effect, correlations of r=.5 between observations, alpha=.05, and compound symmetry of the covariance structure.

For binary outcomes, based on the three repeated observations with a conservative estimate for the assumed correlation of r=0.5 between observations, alpha=.05, sample size of n=50 per treatment arm will have power of 80% to detect odds ratios of the difference between groups ranging from 2.6 to 3.5 (small to medium effects).

Adequacy of sample size will be monitored during the analyses in three ways: (1) assessing sufficiency to estimate the number of model parameters identified by preliminary analyses; (2) examining model fit indices (eg, intra-class correlation coefficient to assess fit of random effects) to ensure data adequately support models generated, and (3) assessing the adequacy to accurately estimate model parameters by generating confidence intervals.

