#### Analysis Plan

We will summarize graphically and numerically the distributions of pain, aching, soreness, tenderness, other symptoms related to lymph fluid accumulation, limb volume differences, BMI, and quality of life as well as covariates (such as medication for pain, age, or education and treatment variable and limb volume and self-care behaviors). The proportion of individuals experiencing pain, aching, soreness, tenderness will be compared between the intervention and control group over time, as will the mean severity ratings and associated quality of life scores. Mean comparisons of number of reported symptoms, limb volume, and BMI will be conducted between the intervention and control group as well as over time.

Bivariate relationships between the variables and treatment group will be assessed using point-biserial correlations and phi coefficients to identify potential covariates for inclusion into statistical models. Linear mixed effects models will be used to analyze continuous outcomes (eg, ratings pain, aching, soreness, tenderness, symptom ratings, and quality of life) and generalized linear mixed models will be used to analyze binary outcomes (presence of pain, aching, soreness, tenderness, and total scores of quality of life). These models will incorporate fixed effects for time, group, and any identified covariates. As indicated by preliminary models to estimate variance effects, models will include random effects for subject-specific slopes and intercepts. A statistically significant fixed effect for group by time interaction will indicate a treatment effect, with the direction of difference determined from mean values. Models will be compared for goodness of fit and modifications to link functions, distributional form, and correlation structure will be made as necessary.

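### The protocol contradicts itself on what is primary and defines the primary endpoint so loosely that no single test decides the trial

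*Protocol article*

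**What the plan says.** **What is primary.** Objectives and Hypotheses states the primary objective as effectiveness "for managing chronic pain, aching, soreness, and tenderness among breast cancer survivors and quality of life related to pain". The matching hypothesis is that "participants in the intervention group will have no or less severe pain, aching, soreness, and tenderness", together with better pain-related quality of life. Outcome Measures differs: "primary measure focuses on pain which is assessed during prior to the intervention and week 12 post-intervention in-person visit", and "Secondary measures include symptoms, limb volume difference by infra-red perometer, BMI, quality of life related to pain". The Abstract (Objective) and the Discussion (Hypothesis) also list quality of life as secondary.

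**The endpoint.** "The primary endpoint for the study is absence of pain or pain reduction reported by the participants at week 12 post-intervention". No symptom item, scale or size of reduction is given. Outcome Measures allows each symptom to be recorded as yes/no and also rated from 0 to 4.

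**The analysis.** The Analysis Plan puts ratings of pain, aching, soreness and tenderness, and quality of life, into linear mixed models. The binary outcomes for generalized linear mixed models are "presence of pain, aching, soreness, tenderness, and total scores of quality of life". A significant group-by-time term is taken as a treatment effect, and no model is named as the primary one.

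**Power.** Sample Size and Power Calculations uses alpha .05 separately for a t test, for continuous mixed models and for binary outcomes. It does not say which belongs to the primary endpoint. The t-test statement refers to a difference "at 8 weeks or at 12 weeks".

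**The concern.** Two things are at stake. The first is consistency. Someone writing the results paper could call quality of life primary or secondary and cite this protocol either way.

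The second is error control. The endpoint has two forms, absence and reduction. The pain construct has four named symptoms, and the analysis models every combination. With no designated test, the result that carries the primary claim can be chosen once the data are in. The .05 used in the power section then no longer describes the chance of a false claim.

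Two smaller slips add to the ambiguity. The power text mentions week 8 although the endpoint is week 12. Quality-of-life totals are listed as binary although Outcome Measures describes the PIQ-6 as giving a T score, and no cut-off is stated.

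**Working it through.** **1. The plan's own power figure.** Inputs from Sample Size and Power Calculations: 60 per arm, 20% attrition, two-sided .05, 90% power, 0.7 SD.

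- Analysed per arm: 60 × 0.8 = 48.
- Detectable difference, normal approximation: (1.960 + 1.282) × √(2/48) = 0.66 SD. With the noncentral t it is 0.67 SD, which rounds to the stated 0.7.
- Power at exactly 0.7 SD with 48 per arm: 92.4% (t).

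The stated figure is reproduced. So is the claim of more than 80% power for a medium effect (0.5 SD taken as medium, r=.5, three or four observations, 48-50 per arm: 85-89%). The odds ratios at n=50 also reproduce: 2.6 gives 80-83% at comparison rates of 0.3-0.5, and 3.5 gives 81% at a rate of 0.1. All of these hold for a test that has the whole .05 to itself.

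**2. Counting the candidate tests.**

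- Narrowest reading, one pain outcome tested for absence and for reduction: 2.
- Four symptoms on one scale: 4.
- Four symptoms × presence and severity: 4 × 2 = 8.
- The eight plus quality of life: 9.

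**3. Chance of at least one p<.05 when nothing differs.** For k independent tests it is 1 − 0.95^k. For correlated tests, k equicorrelated normal statistics were simulated (1,000,000 sets). The correlations are assumptions: the r=.5 in the power section is between repeated observations, not between outcomes.

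| k | independent | r=.5 | r=.7 | r=.8 | r=.9 |
|---|---|---|---|---|---|
| 2 | 9.8% | 9.1% | 8.4% | 7.8% | 7.0% |
| 4 | 18.5% | 15.6% | 13.1% | 11.4% | 9.4% |
| 8 | 33.7% | 25.1% | 19.0% | 15.7% | 12.0% |
| 9 | 37.0% | 27.0% | 20.3% | 16.5% | 12.3% |

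Independence is the upper value, because these symptoms are likely to be positively correlated. Presence and severity of one item are also linked by construction, since a rating of 0 means the symptom is absent. A single common correlation is therefore only a rough model.

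The table counts differences in either direction. Counting only results that favour the intervention (nominal 2.5%), nine tests give 20.5% if independent, 13.6% at r=.5 and 8.3% at r=.8.

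**4. What designation is worth.** If all nine stayed primary with a Bonferroni split, each would be tested at .05/9 = .0056. Power for 0.7 SD with 48 per arm would fall to 72%. The difference detectable with 90% power would rise to 0.84 SD, and holding 0.7 SD at 90% would need 70 analysed per arm. One designated test at .05 keeps 92%.

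**The case against.** The strongest reply is that pain is one construct here. Design defines chronic pain as covering aching, tenderness and soreness, Study Population and Outcome Measures group them in the same way, and the endpoint section fixes week 12. On that reading only absence and reduction remain, and the inflation is about 7-10%. This stands as the lower end of the range. It does not remove the problem, because no rule combines the four items and the Analysis Plan models them separately.

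A reader might infer that any one of eight or nine significant results makes the trial positive, so that the error rate is far above 5%. The document does not say so. The group-by-time sentence describes how a model will be read and is not a rule for trial success. The primary hypothesis joins its parts with *and*; if every part were required, error would not be inflated at all. The document leaves this open, so the inflation is conditional on a choice made after the results.

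A reader might also treat the mention of week 8 as a second chance at success. It stands only in a power statement, and no separate week-8 test is planned. It is a mismatch to correct, not another source of error.

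The absence of a multiplicity rule is not a fault in itself, since an analysis plan that is not shown may contain one. It is likewise too strong to say that the analysis ignores the endpoint: absence maps to the presence model and reduction to the ratings model. What is missing is the statement of which one decides.

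Finally, the Discussion gives estimating an effect size for a later multi-center trial as one aim. That softens the consequence. But the Abstract and the Introduction announce an efficacy evaluation, and the sample size is justified by a test at .05 with 90% power.

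**Conclusion.** Wrong as written. Quality of life cannot be both in the primary objective and a secondary outcome. An endpoint of absence or reduction, with no item, scale or size, does not identify a test. The week-8 wording and the binary listing of quality-of-life totals conflict with the document's own endpoint and instrument description.

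If the deciding test can be picked after the results, the chance of at least one false positive exceeds .05. It is about 7% (r=.9) to 10% (independent) on the narrowest reading, about 12% to 34% for eight tests, and about 12% to 37% for nine. These figures rest on assumed correlations between outcomes, which the document does not give, and on no true difference in any outcome. They do not show that the trial's error rate is any one of these values, because the document never states what result would count as success.

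**What to change.** - Designate one pain outcome, on one scale, at week 12, as the single primary test at two-sided .05, and state the model contrast that tests it. A severity score built from the four 0-4 ratings already collected is one possibility; the choice of score is the sponsor's.
- Make the other form (presence or severity), the individual items and quality of life secondary. Give quality of life that same status in the Abstract, Objectives and Hypotheses, Outcome Measures and the Discussion.
- Refer the power statement to week 12 only.
- Analyse the PIQ-6 T score in the linear mixed model only and remove it from the binary list.

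The cost is wording, plus the fact that outcomes not chosen can no longer carry the primary claim. No extra participants are needed for the stated t test: one designated comparison keeps about 92% power for 0.7 SD with 48 per arm. Power for the chosen score and contrast should be confirmed once they are named.
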